# 1. SCIENTIFIC JUSTIFICATION OF THE RESEARCH

## Background

Mosquito-borne diseases are those spread by the bite of an infected mosquito. *Aedes* spp. can transmit dengue virus (DENV), chikungunya virus (CHIKV), zika virus and yellow fever virus. In Thailand, dengue and chikungunya pose a significant public health concern, particularly among adolescents. Dengue fever is a disease that has no specific antiviral treatment but is managed supportively. Currently, the care and treatment of dengue fever patients has become much more effective. However, it is still observed that the mortality rate is approximately 0.1 to 0.5 percent, resulting in significant losses. Chikungunya is a viral illness characterized by sudden onset of high fever, joint pain, rash and myalgia. It can cause persistent joint pain that may last for months or years among adults but mild joint pain in children. However, neurological complication is reported frequently among children. There is also no specific antiviral treatment for chikungunya, so management focuses on supportive care to alleviate symptoms.

Prevention of dengue and chikungunya infection involves measures to reduce mosquito breeding/oviposition sites, and personal protective measures, including the use of mosquito repellents and wearing long-sleeved clothing, are also recommended. Currently, dengue vaccines are available and can prevent infection and decrease severity, but remain controversial because of potential increased severity upon infection with DENV in naïve individuals – the phenomenon known as Antibody-dependent enhancement. There is no available chikungunya vaccine.

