## 2. **OBJECTIVES**

### **Primary objective:**

To address the extent to which (satellite-) predicted and empirically validated mosquito abundance and mapped transport/mobility connectedness among Khwaeng do associate with DENV and CHIKV exposure as measured by sero-positivity. Coupled with a detailed geographic information system (GIS) of Bangkok, including fine scale meteorological data, will subsequently enable fine scale agent-based simulation models to test *in silico* the efficacy of implementing vector control in a variety of locations.

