## 4. **STUDY POPULATION AND SOURCE OF RECRUITMENT**

#### 4.1. Inclusion criteria

1. Aged 10-15 years old from schools characterised by the environmental and centrality typology.
2. Signed informed consent.

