#### 4.2. Exclusion criteria

1. Suffering from any concurrent infection or with any physical or mental disability.
2. Refusal to participate.

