#### ***For sero-conversion study (specific data collection):***

For each participating child, the age, gender, history of infection/ dengue vaccination, school name and address, house address and RDT test results for both dengue and Chikungunya will be written on the Case Report Form (CRF) immediately following the test. Information on age, sex and history of infection/ dengue vaccination will be obtained. We will also collect the school and place of residence coordinates (longitude & latitude), which will be subsequently classified in one of the four typologies Central+/Environmental+, Central+/Environmental-, Central-/Environment+, Central-/Environment aggregated to the scale of the grids as shown in Figures 1 & 2 and the coordinates information then erased.

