| Personal data: last name, first name, e-mail, telephone number, postal address, guardian/trusted person... | Contacting participants to set up appointments, returning overall and/or individual results, maintaining communication with participants during the research, exercising participants' rights. |

| Data available to investigators and scientists for research                                                                                |                                                                                                                       |
|--------------------------------------------------------------------------------------------------------------------------------------------|-----------------------------------------------------------------------------------------------------------------------|
| Data                                                                                                                                       | Justification                                                                                                         |
| Identification data : participant code                                                                                              | Linking a participant's data set and samples                                                                          |
| Demographic data : age, gender, level of instruction,                                                                               | Describe the study population                                                                                         |
| Medical data : history of dengue and chikungunya infection, dengue vaccination and RDT test results for both dengue and chikungunya | Describe the general clinical pattern of the subjects studied for sero-conversion study.                              |
| Localisation : school name and address, home address, environmental typology                                                        | Connectivity and environmental typology of the area within which the individual goes to school and lives              |
| Assessment on dengue and chikungunya among parents                                                                                  | Describe the knowledge, attitude, and practice about mosquito-borne disease, control measures, and vaccine acceptance |

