## 9. STATISTICAL CONSIDERATIONS

Sample size:

Based on the preliminary data showing a difference in prevalence rates according to school centrality and environmental typology (approximately 26% vs 15%), we estimate a necessary sample size of ~210 children for each of the four typologies (Central+/Environmental+, Central+/Environmental-, Central-/Environmental+, Central-/Environmental-).

Sample size was calculated as follows [17]

$$n = (Z_{\alpha/2} + Z_{\beta})^2 \cdot [p_0(1 - p_0) + p_1(1 - p_1)] (p_0 - p_1)^2$$

Where n is the required sample size per treatment arm,  $Z_{\alpha}$  and  $Z_{\beta}$  are constants set by convention according to the accepted  $\alpha$  error and whether a one-sided or two-sided effect,  $p_0$  is the proportion sero-positive in area type 0 (ie Central + or Environment +), and  $p_1$  the proportion areas type 2 (Central – or Environment –).

Assuming a  $p < 0.05$  as acceptable and a study with 90% power, the following constant values are:  $Z_{\alpha/2} = 1.96$  and  $Z_{\beta} = 0.84$ .

Because our preliminary data indicated variation within school centrality and environmental typology, (coefficient of variation ranging from 0.6-1), we used the following formula to estimate the number of different sites for each typology.

$$\text{Site number per typology} = 1 + (Z_{\alpha/2} + Z_{\beta})^2 \cdot [p_0(1 - p_0)/n + p_1(1 - p_1)/n + k^2(p_0^2 + p_1^2)] (p_0 - p_1)^2$$

Where k is the coefficient of variation and n the number of individuals as calculated above. Using  $n=210$  and  $k=0.6$  to 1, we would need at least two and optimally three schools per environmental typology with 80-100 children per school.

Sero-positivity (as defined by the manufacturers instructions) will be analysed by logistic regression with age, sex and centrality (high vs. low) and environmental typology (Open vs Dense) as explanatory variables using R. School mosquito densities will also be included as an explanatory variable. In the subset of individuals collecting mosquitoes in the homes will be taken into account in a separate analysis. Mosquito densities will also be analysed with respect to the environmental typology and meteorological parameters.

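### The dengue exposure model leaves out the recorded vaccination history, so vaccine-induced IgG, if it occurs and uptake differs by area, can distort the area association

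*Protocol*

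**What the plan says.** The primary objective (section 2) asks how far mosquito abundance and connectedness "do associate with DENV and CHIKV exposure as measured by sero-positivity". A positive test therefore stands for exposure.

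Eligibility does not depend on vaccination. The inclusion criteria (section 4.1) are "Aged 10-15 years old from schools characterised by the environmental and centrality typology" and signed consent. The exclusion criteria (section 4.2) are "Suffering from any concurrent infection or with any physical or mental disability" and refusal.

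Vaccination is recorded. Section 7.1 puts on the case report form "history of infection/ dengue vaccination, school name and address, house address and RDT test results", and the data table in section 7.2 lists "history of dengue and chikungunya infection, dengue vaccination and RDT test results for both dengue and chikungunya".

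Section 9 then fixes the model: "Sero-positivity (as defined by the manufacturers instructions) will be analysed by logistic regression with age, sex and centrality", followed by environmental typology, with school mosquito density added as a further term. It names no vaccination term, restriction or sensitivity analysis.

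On availability the protocol points two ways. The Background says "Currently, dengue vaccines are available and can prevent infection and decrease severity", while section 5.3 describes one named product as still being assessed for authorisation in Thailand.

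**The concern.** If vaccination can produce IgG that this kit detects, a vaccinated child who was never infected would enter the model as exposed. The comparison is between area types, so the effect depends on uptake by area. Higher uptake in the high-exposure areas would add to the contrast, and higher uptake in the low-exposure areas would shrink it. Age and sex cannot be relied on to remove this, and no socio-economic variable is in the model.

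A second consequence needs no uptake gap. Section 5.3 offers the seroprevalence figures to health authorities as a guide for vaccine implementation, and vaccine-induced positives would raise the dengue figure even if uptake were the same everywhere.

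A related but lesser point is time. Section 5 uses IgG as a marker of previous infection, but section 7.1 lists only the location of school and residence, not the years spent there. A recent mover is classified under an area where the infection may not have happened, which would mainly dilute the contrast.

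**Working it through.** **Inputs from the protocol**
- Planning rates 26% and 15%, difference 11 points, about 210 children per typology (section 9).
- Pilot dengue seroprevalence at 10-15 years: 37.2% (section 1, Background).
- 1000 children over four typologies (section 5.1): 1000/4 = 250 each.

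**Assumptions, because the documents give no figure**
- u: vaccine uptake in an area type.
- s: the chance that a vaccinated, never-infected child tests IgG-positive.
- Uptake is independent of previous infection and is reported correctly.

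**Step 1. The plan's own figure.** With the squared difference as divisor, (1.96 + 0.84)² × [0.26 × 0.74 + 0.15 × 0.85] / 0.11² = 7.84 × 0.3199 / 0.0121 = 207, which agrees with about 210. The 0.84 used here corresponds to 80% power, although section 9 labels it 90%. That is a separate matter. The 11 points are the yardstick below.

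**Step 2. False difference when true exposure is equal.** Apparent prevalence = p + (1 − p) × u × s. With the same p in areas A and B, the difference is (1 − p) × s × (uA − uB). With p = 0.372 and 1 − p = 0.628:

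| Uptake A vs B | s = 1 | Share of 11 points | s = 0.5 |
|---|---|---|---|
| equal | 0 | 0% | 0 |
| 2% vs 0% | 0.628 × 0.02 = 1.3 points | 11% | 0.6 |
| 5% vs 0% | 0.628 × 0.05 = 3.1 points | 29% | 1.6 |
| 10% vs 2% | 0.628 × 0.08 = 5.0 points | 46% | 2.5 |

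A lower p leaves more children to convert. At 5% vs 0% and s = 1 the result is 0.74 × 0.05 = 3.7 points at p = 26%, and 0.85 × 0.05 = 4.25 points at p = 15%.

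**Step 3. Can vaccination alone produce the planning effect?** At p = 37.2% this needs an uptake gap of 0.11 / 0.628 = 17.5 points at s = 1, or 35 points at s = 0.5.

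**Step 4. Masking.** Take true rates of 26% vs 15%, with 10% uptake only in the low-exposure areas and s = 1. The low rate becomes 0.15 + 0.85 × 0.10 = 23.5%, and the 11 points fall to 2.5.

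**Step 5. Level of seroprevalence.** Uptake of 5% everywhere with s = 1 moves 37.2% to 0.372 + 0.628 × 0.05 = 40.3%, with no area difference created.

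**Step 6. Cost of restricting to unvaccinated children.** 250 × (1 − u) ≥ 210 holds up to u = 1 − 210/250 = 16%.

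**Step 7. Limit of the restriction.** If vaccinees were all previously infected, there would be no false positives to remove, and exclusion would discard true ones. At p = 37.2% and 5% uptake, the remaining prevalence is (0.372 − 0.05) / 0.95 = 33.9%, which is 3.3 points too low. This is the extreme case, but it is as large as the 3.1 points in step 2.

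**The case against.** **This is material for a statistical analysis plan.** Analysis sets and sensitivity analyses often sit there, and that document is not at hand. The protocol does record the variable and does not say that its list of model terms is closed. This lowers the weight of the point but does not remove it. The protocol itself fixes the outcome definition, the eligibility and the model terms, and an analyst who follows them would count a vaccine-induced positive as exposure.

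**Uptake may be negligible.** No uptake figure is given, and section 5.3 suggests that at least one product was not yet in routine use. No passage relates uptake to area type: Table 1 links socio-economic variables to dengue cases, not to vaccination. No passage says that vaccination turns this kit positive. All of this stands, so the size is unknown and could be near zero.

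**Excluding vaccinees is not clearly better.** Vaccinees may be more often previously infected. This also stands (step 7), and it is why one analysis alone is not enough.

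**Stronger readings.** A reader might infer that section 7.2 reserves vaccination history for description only. It does not: the same table row, with the same justification, covers the rapid test results, which are the primary outcome and go into the regression. A reader might also infer that area differences in uptake will show up as exposure differences. The documents support only that they can. Finally, a reader might conclude that the case report form omits length of residence. The form is not shown; only the list in section 7.1 is.

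**Conclusion.** The omission is plain on the text: vaccination is collected, vaccinated children are eligible, and the stated dengue model does not use the information. The consequence is conditional. It needs vaccine-induced positivity on this test and, for the area association, unequal uptake. Under certain positivity and a 37.2% infection rate, the range is 0 to 5.0 points over the scenarios shown, and half that if s = 0.5. Vaccination alone is unlikely to produce the whole planning effect unless uptake gaps are large, but a modest gap could add to it or hide part of it.

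The point concerns dengue only, since the Background states that no chikungunya vaccine is available. The time-at-address issue is secondary. The documents give no mobility figure, so its size cannot be estimated.

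**What to change.** In section 9, state that:
- the main dengue model is fitted in children with no reported dengue vaccine dose;
- uptake, and seropositivity among vaccinated children, are reported by typology;
- the all-children model with a vaccination term is given as a sensitivity analysis, next to the model as now written. If every vaccinee tests positive, the term cannot be estimated and that model reduces to the restricted one. The version without the term is then what shows the effect of leaving vaccinees out.

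The data are already planned, so the cost is a few lines of text and a small loss of sample. The target of 210 per typology is kept up to about 16% uptake. Restriction may also remove vaccinees who were truly infected, which is why the analyses should be read together.

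As a cheap addition, record years at the present school and home, and repeat the analysis in long-term attenders and residents. This has to be in place before enrolment: coordinates are erased, paper forms are destroyed and participants become unidentifiable (sections 7.1, 7.2 and 10.2), so it cannot be recovered later.

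### The named logistic regression has no school term although school typology is fixed within 8-12 schools; on the protocol's own between-school variation, its nominal 5% tests would be falsely positive about half to three quarters of the time

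*Protocol*

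**What the plan says.** Section 9 of the Protocol (Statistical considerations) names the primary model: sero-positivity "will be analysed by logistic regression with age, sex and centrality (high vs. low) and environmental typology (Open vs Dense) as explanatory variables". It adds one school-level covariate: "School mosquito densities will also be included as an explanatory variable". It does not mention a random effect for school, generalised estimating equations, a cluster-robust variance or a school-level analysis, and neither does any other section. Section 7.2 (Data management) refers forward to this text for the statistical analysis, so it is the operative specification.

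The sizing paragraphs of the same section do recognise clustering. They say that "our preliminary data indicated variation within school centrality and environmental typology, (coefficient of variation ranging from 0.6-1"), apply a formula taken from a reference on cluster-randomised trials, and conclude that "we would need at least two and optimally three schools per environmental typology with 80-100 children per school".

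Sections 4.3 and 5.1 select schools by typology: 2-3 schools in each of four area types, 8-12 in all, and 1000 children.

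**The concern.** A variable that is constant within a school can only be compared between schools. The information on school centrality, school environment and school mosquito density is therefore limited by the 8-12 schools, however many children are tested in each. A logistic regression on individual children with no school term takes its standard errors from about 1000 supposedly independent observations. Section 9 says that prevalence differs widely between sites of the same type, and then names a model that assumes no such difference once the covariates are fitted.

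The association of centrality and environment with sero-positivity is the primary objective (section 2). It is also meant to feed simulation models of where to apply vector control. Under the named model, ordinary differences between schools would often be reported as effects of centrality or environment.

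**Working it through.** **Inputs.** From section 9: prevalences "approximately 26% vs 15"%, two-sided 1.96, Zβ = 0.84, and k = 0.6 to 1. From sections 4.3 and 5.1: 8-12 schools and 1000 children, so 12 schools of about 83 or 8 schools of 125. Assumed: a mean prevalence of about 20%, the midpoint of 26% and 15% (20.5%).

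**The plan's own figure.** Reading the last factor of the printed formula as a divisor:

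n = (1.96 + 0.84)² × [0.26 × 0.74 + 0.15 × 0.85] / 0.11² = 7.84 × 0.3199 / 0.0121 = 207.

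The stated 210 or so per typology reproduces. (A Zβ of 0.84 corresponds to 80% power, not the 90% in the text. That is a separate matter.) This n takes no account of clustering.

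**Design effect from the plan's k.** ICC = k² × p / (1 − p), and design effect = 1 + (m − 1) × ICC. At p = 0.20 and m = 83:

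| k | ICC | Design effect | SE too small by (square root) | 1000 children worth |
|---|---|---|---|---|
| 0.6 | 0.36 × 0.25 = 0.09 | 1 + 82 × 0.09 = 8.4 | 2.9 | 119 |
| 1 | 1 × 0.25 = 0.25 | 1 + 82 × 0.25 = 21.5 | 4.6 | 47 |

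**False-positive rate.** The approximation is 2 × [1 − Φ(1.96 / √design effect)]. It gives 50% (k = 0.6) and 67% (k = 1) with 83 per school. With 125 per school the design effects are 12.2 and 32, and the rates 57% and 73%.

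Simulation under no effect (3000 runs per scenario, beta-distributed school prevalences with mean 20.5%, logistic regression on centrality and environment, nominal 5%) agrees:

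| Schools × children | k | Centrality term significant | Either typology term significant | School-level analysis, t reference |
|---|---|---|---|---|
| 12 × 83 | 0.6 | 52% | 76% | 5% |
| 12 × 83 | 1 | 70% | 91% | 4% |
| 8 × 125 | 0.6 | 59% | 83% | 6% |
| 8 × 125 | 1 | 74% | 92% | 4% |

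Repeat simulations at 20% and 20.5% prevalence gave rates within about 3 percentage points of these for the centrality term. With k = 0 the named model holds its level (about 5%), so the excess comes from between-school variation alone. Adding a school mosquito covariate with no effect leaves the rates at 50% and 69% with 12 schools, because it does not absorb the remaining differences between schools. The simulations omit age and sex, which would help only as far as they explain differences between schools.

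**Sensitivity.**
- Smaller k (assumed): 8-9% at k = 0.1, 15-20% at k = 0.2 and about 20-26% at k = 0.25.
- Higher prevalence: the pilot found 37.2% at ages 10-15 (section 1). At k = 0.6 and 83 per school, ICC = 0.36 × 0.372 / 0.628 = 0.213, design effect 18.5, approximate error 65%.
- Low chikungunya prevalence: section 1 cites 2.6% in central Thailand. With the same k (assumed) and 83 per school, ICC is 0.010-0.027, design effect 1.8-3.2, approximate error 14-27%.

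**The case against.** The strongest reply is that the Protocol says only logistic regression and lists covariates. A random-intercept model would fit those words, and the variance structure is often left to an analysis plan. That would carry weight in a section silent on clustering. Here the section quantifies between-site variation, uses a cluster formula to choose the number of schools, and then lists the model terms without school. Followed as written, it gives wrong standard errors.

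Four narrower points stand and limit the size:
- **Home typology.** Homes are also classified (section 7.1), and section 9 does not say whether home or school typology enters the model. Home typology varies within schools, so its inflation is smaller. With 12 schools of 83, 20% prevalence and k = 0.6-1, a simulation gave about 7% if half the children live in the same type of area as their school, 17-35% at 70% and 41-61% at 90%. These concordance levels are assumptions.
- **Chikungunya.** If prevalence is near 2.6%, standard errors are only about 1.3-1.8 times too small.
- **What k measures.** The Protocol does not say how k was estimated, or whether sampling error and age were removed. At 20% prevalence, binomial noise alone gives a raw coefficient of variation of √(0.8 / (0.2 × m)): 1.0 with 4 children per site and 0.60 with 11. The pilot had 272 children aged 3-15, with 6.5% positive at 3-9 and 37.2% at 10-15, so the true k may be lower. The Protocol nevertheless uses it as between-site variation, and an assumed k of 0.2 still triples the error rate or worse.
- **Power.** The correction exposes a weakness that the named model hides; this belongs in its cost.

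**Conclusion.** The concern holds. For school-level terms, the model in section 9 is inconsistent with the design described in the same section. Taking the Protocol's k of 0.6-1 at face value, with prevalence near 20% and 8-12 schools, each typology test at nominal 5% would be falsely positive in about 50-75% of studies, and at least one of the two in about 76-92%. A smaller true k, low chikungunya prevalence or a home-typology term reduces the inflation. It is close to nominal only if between-school variation is negligible, or for a home term that is unrelated to school typology. This must be corrected before analysis, because it decides whether the primary finding can be believed.

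**What to change.** Rewrite the analysis paragraph of section 9 so that school is accounted for in every typology and mosquito-density contrast:
- Either a mixed-effects logistic regression with a random school intercept and small-sample (t) inference, which can also carry home typology as an individual-level term;
- or a school-level regression of age- and sex-adjusted prevalence on centrality and environment with a t reference. Residual degrees of freedom are 12 − 3 = 9 with 12 schools or 8 − 3 = 5 with 8, and one fewer (8 or 4) once mosquito density is included.

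Uncorrected sandwich standard errors are not enough with 8-12 clusters. State whether each typology term refers to home or school, and give school-clustered confidence intervals for the seroprevalence rates.

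The change is to wording only and needs no new data. The price is wider intervals. At k = 0.6, a valid school-level test of 26% against 15% has about 13% power with 8 schools and 23% with 12. That limit is already in the design: with n = 210 and the last factor read as a divisor, the Protocol's own site formula gives 1 + 7.84 × [0.3199/210 + 0.36 × (0.26² + 0.15²)] / 0.0121 = 23 schools per typology at k = 0.6, and 60 at k = 1, against the two or three planned. The sponsor should state this limit alongside the corrected model.
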